## Data analysis

Descriptive statistics will be provided for demographic characteristics and outcome variables, including means and standard deviations for continuous variables and proportions for categorical variables. Independent sample t-tests and chi-square analyses will be conducted to evaluate potential baseline differences between participants assigned to the experimental and control groups to determine preliminary efficacy. The qualitative data collected in the final interview will be included in the analysis. For the data collected during the lab experiment, we will opt for a multimodal analytical approach. Behavioral and physiological data regarding sexual cognitions and interoception will be collected to explore underlying psychological and neurological processes and potential changes resulting from the intervention. Hence, for the within-subject factors (such as multiple time points or conditions in the ERP or thermal response experiments), rmANOVAs or Linear Mixed Effects (LME) models will be used for detecting overall differences across these conditions. Regression analyses will help in predicting outcomes, and correlations can offer insights into the strength and direction of associations. GMLL will allow us to model the random effects of individuals, accounting for the correlation among repeated observations and providing subject-specific insights. Differences between the experimental and control groups regarding secondary outcomes will also be analyzed. We will comply with the intention-to-treat (ITT) principle for comparisons between treatment groups.

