After completing the online baseline (T1) assessment, participants meeting eligibility criteria will be registered and randomized, following an appointment with the assigned research member (Psychologist) to provide program access, examine the program’s framework (Figure 2), present the baseline findings, and establish therapeutic goals. The primary outcomes of this pilot trial are acceptability, usability (System Usability Scale (SUS) (Bangor, Kortum, & Miller, 2008) and feasibility measures (i.e., recruitment, randomization, retention, and adherence rates). Acceptability will be assessed in postintervention semistructured interviews. Secondary outcomes will evaluate preliminary efficacy on sexual beliefs (Sexual Dysfunctional Beliefs Questionnaire (SDBQ); Nobre & Pinto‐Gouveia, 2003), sexual satisfaction (Global Measure of Sexual Satisfaction (GMSEX); Lawrance & Byers, 1995), function (Index of Erectile Function (IIEF); Rosen et al., 1997b); and Female Sexual Functioning Index (FSFI); Rosen et al., 1997a), pleasure (Sexual Pleasure Scale (SPS); Sanchez, Crocker, & Boike, 2005) and distress (Female Sexual Distress Scale-Revised (FSDS-R); Derogatis et al., 2002). Additionally, participants will complete a self-report questionnaire to provide their sociodemographic and sexuality-related behavioral data, including age, gender, relationship status, religion, education, sexual orientation, and frequency of sexual activities. Changes in potential transdiagnostic factors, namely interoceptive awareness (Multidimensional Assessment of Interoceptive Awareness (MAIA; Mehling et al., 2012), trauma screening questionnaire (Posttraumatic Stress Disorder Checklist for DSM-5 (PCL-5; Weathers et al., 2013), questions about negative sexual experiences, mindfulness (Cognitive and Affective Mindfulness Scale-Revised (CAMS-R); Feldman et al., 2007), quality of life (World Health Organization Quality of Life: Brief Version (WHOQOL-BREF); The Whoqol, 1998), psychopathology (BSI-18; Derogatis, 2001), and therapeutic outcomes (Outcome Questionnaire (OQ-45); Lambert et al., 2004), will be assessed. As mentioned before, a subsample of participants will be invited to on-site laboratory sessions (at T1 and T2). Using a multimodal approach that combines EEG, behavioral tasks, thermal imaging, and self-report measures on affect (Positive and Negative Affect Schedule (PANAS; Watson, Clark, & Tellegen, 1988) and automatic thoughts (Sexual Modes Questionnaire - Thoughts Subscale (QMS; Nobre & Pinto‐Gouveia, 2003), this complementary part of the study will allow us to explore how brain activity, implicit cognitions, and interoceptive awareness contribute to intervention-related changes in sexual functioning and perception.

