
Participants will be instructed to conclude each module within a week. Within 24 hours before the pre-defined timeframe for module completion, the assigned research member will evaluate participants’ progress based on the reported results and decide whether participants will have access to the subsequent module. Such results will be shared with the participants, and, if deemed required, further instructions will be provided on the steps to proceed to the forthcoming module. The intervention’s initial effectiveness will be evaluated upon program completion at posttest (T2 for arm 1 and T1rep for arm 2), utilizing the aforementioned measures, and a final interview for debriefing, user-experience and acceptability assessment.

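### The Data analysis section ties preliminary efficacy to tests of baseline differences, which precede randomisation and cannot show an effect

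*Protocol article*

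**What the plan says.** The second sentence of Data analysis begins: "Independent sample t-tests and chi-square analyses will be conducted to evaluate potential baseline differences". The full purpose that it gives for those tests is to "evaluate potential baseline differences between participants assigned to the experimental and control groups to determine preliminary efficacy".

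Three other statements bear on it:

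- Intervention delivery and assessment, on the order of events: "After completing the online baseline (T1) assessment, participants meeting eligibility criteria will be registered and randomized".
- The same section, on which outcomes carry efficacy: "Secondary outcomes will evaluate preliminary efficacy on sexual beliefs", with satisfaction, function, pleasure and distress listed after it. On timing, it says that "initial effectiveness will be evaluated upon program completion at posttest (T2 for arm 1 and T1rep for arm 2".
- Data analysis, near its end: "Differences between the experimental and control groups regarding secondary outcomes will also be analyzed". The next sentence commits treatment-group comparisons to intention to treat. Neither sentence gives a test, model, time point or covariate.

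**The concern.** A test of baseline differences between randomised arms asks whether the allocation produced an imbalance. Under proper randomisation the answer is known in advance: any imbalance is chance. Such a test contains no post-treatment data and cannot determine efficacy, preliminary or otherwise.

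This is a stated purpose that is wrong, not a detail left out. The article's Introduction justifies publication partly by pre-specifying all hypotheses and analyses. The section on participants and eligibility criteria says the pilot should supply effect sizes for sizing the definitive trial. The between-arm effect estimate is therefore a main product of the pilot, and the only sentence that names a between-arm test for it points to T1.

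**Working it through.** **Inputs from the protocol article.** 35 per arm, 1:1 allocation, N = 70 (2 × 35 = 70, which agrees). Anticipated retention is 70–75%, so 0.70 × 35 = 24.5 to 0.75 × 35 = 26.25 completers per arm. T1 precedes randomisation; the post-test is T2 in arm 1 and T1rep in arm 2.

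**Assumptions not in the article.** Two-sided 5% level, SD 1, T1 to post-test correlation 0.5, true standardised effect d from 0 to 1.2. The article gives no level, power, SD or effect size, so it has no power figure to reproduce.

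**Step 1: the argument.** The treatment effect enters only after T1. The distribution of the T1 difference between arms is therefore the same whatever the effect is, and the null hypothesis at T1 is true by design. The rejection rate must equal the test level.

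**Step 2: numerical check.** 20,000 simulated trials per effect size, 35 per arm, independent t-test at each time point. The last column uses the power formula for two means at 24.5 to 26.25 per arm.

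| True d | Rejects at T1 | Rejects at post-test | Formula, post-test, 70–75% retained |
|---|---|---|---|
| 0 | 4.9% | 4.8% | 5% |
| 0.3 | 4.8% | 23% | 18–19% |
| 0.5 | 4.9% | 54% | 42–44% |
| 0.8 | 5.2% | 91% | 80–83% |
| 1.2 | 4.9% | 99.8% | 99% |

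The same formula at 35 per arm gives 24%, 55%, 92% and 99.9% for d = 0.3 to 1.2, close to the simulation. The T1 column is flat; only the post-test comparison responds to the effect.

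**Step 3: what adjustment for T1 would give.** Adjusting the post-test difference for the T1 value multiplies its variance by 1 − r².

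- r = 0.5 (assumed): 1 − 0.25 = 0.75; interval width factor √0.75 = 0.87.
- r = 0.7 (assumed): 1 − 0.49 = 0.51; interval width factor √0.51 = 0.71.

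This measures the benefit of the proposed analysis. It does not measure the size of the error in the sentence.

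**The case against.** The strongest defence is that the sentence is an editing slip: a routine baseline check and an efficacy comparison run together. The rest of the article supports that. It assigns efficacy to the secondary outcomes, places the evaluation at post-test, and plans a between-arm comparison under intention to treat. This stands, and it limits the consequence. It does not rescue the sentence, because a reader cannot recover which efficacy test was meant. A separate analysis plan could add detail, but it would not correct a published statement that gives a named test the wrong purpose.

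A second defence is that this is a pilot. The primary outcomes are acceptability, usability and feasibility, and the article says that it is not powered for efficacy. That also stands and lowers the weight of the point. On the other side, the Discussion lists preliminary efficacy among the primary objectives, and effect sizes are wanted for the next trial.

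Three stronger readings are tempting, and the document does not support them:

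- **That no post-treatment efficacy analysis is planned.** One is planned; only its method is not named.
- **That the post-test comparison will be unadjusted.** The article is silent on T1 adjustment, and model form is commonly left to the analysis plan.
- **That allowing repeated-measures ANOVA conflicts with intention to treat.** The statement that "rmANOVAs or Linear Mixed Effects (LME) models will be used for detecting overall differences across these conditions" concerns within-subject factors in the laboratory data. That subsample of 20 is drawn from the intervention group, while the intention-to-treat sentence covers comparisons between treatment groups. The two do not meet.

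**Conclusion.** The point holds in a limited form. One sentence gives baseline tests a purpose that they cannot serve, and it contradicts the article's own statement that effectiveness is judged at T2/T1rep. As efficacy evidence the named tests are worthless: about 5% rejections at any true effect, given a 5% level and sound randomisation. The flat rate does not depend on the assumed SD or correlation; the post-test figures do depend on the stated assumptions.

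The weight is moderate. The error concerns a secondary, unpowered aim, and a post-treatment comparison is planned elsewhere in the text. It should still be corrected, because the effect estimates are meant to inform the definitive trial.

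**What to change.** Split the sentence in Data analysis into two statements:

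1. Baseline characteristics are described by randomised arm (means and SDs, or proportions), without significance tests and without use as evidence of efficacy.
2. Preliminary efficacy is the between-arm difference in each secondary outcome at T2 (arm 1) and T1rep (arm 2), analysed by randomised arm and adjusted for the T1 value by ANCOVA or a linear mixed model. It is reported as an estimate with a 95% confidence interval.

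The interval suits a pilot that disclaims power for efficacy, and it is what the planners of the definitive trial will need. The laboratory analyses need no change on this account. The cost is a change of wording: T1 and post-test values are already to be collected, and the T1 adjustment improves precision without further participants.

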## Results

The results on acceptability, usability, feasibility, and preliminary efficacy of FULLSENSE are expected in the second semester of 2025. Study results will be published in open-access venues according to the Consolidated Standards of Reporting Trials of Electronic and Mobile Health Applications and Online Telehealth guidelines (Eysenbach, 2011). We anticipate that it will be feasible to scale up to parent RCTs and that FULLSENSE will effectively promote positive changes in secondary outcomes.

## Discussion

Sexual dysfunction is often associated with increased levels of psychological distress and sexual dissatisfaction (Handy & Meston, 2018). Online sexual health programs offer a promising avenue for addressing these challenges, providing unparalleled accessibility and scalability. FULLSENSE, a program employing a mixed-methods approach to encompass diverse sexual dysfunction, aims to deepen our understanding of the impact of such interventions.

This study evaluates the feasibility, acceptability, and preliminary efficacy of FULLSENSE, an online intervention designed for adults experiencing sexual dysfunction. This study is designed as a randomized controlled trial (RCT) comparing FULLSENSE to a waiting-list control (WLC) condition. The primary objectives are to assess the feasibility and preliminary efficacy of FULLSENSE in individuals reporting distressful sexual complaints. We hypothesize that FULLSENSE will demonstrate acceptability, usability, feasibility, and preliminary signs of efficacy in improving sexual health, satisfaction, and pleasure. Furthermore, this pilot feasibility trial aims to validate the chosen methodology, ensuring its coherence with participants’ expectations and needs. Individuals experiencing sexual dysfunction often report distress, sexual dissatisfaction, isolation, and other negative impacts on their well-being (Vasconcelos et al., 2024). Effective, accessible, and engaging biopsychosocial interventions are crucial to address these unmet needs.

Digital health interventions (Avery-Clark, Weiner, & Adams-Clark, 2019; Banbury et al., 2024; Benzo et al., 2022; Borgmann et al., 2023; Bossio, Higano, & Brotto, 2021; Bossio et al., 2019; Brotto, Stephenson, & Zippan, 2022; Brotto et al., 2017; 2021; 2025; Van Lankveld, 2016; Zippan, Stephenson, & Brotto, 2020) like FULLSENSE offer a promising avenue for enhancing access to and broadening the dissemination of supportive care. Unlike earlier programs, FULLSENSE does not target a specific population or sexual dysfunction, thus embracing a more comprehensive approach to promoting sexual health. By adopting a positive approach to sexuality that includes pleasure, FULLSENSE addresses a crucial, often neglected aspect of sexual health (Van Lankveld et al., 2021) and aims to be an inclusive program, suitable for all people. An additional distinctive feature pertains to its delivery format, providing a safe and comfortable environment for exploring sensitive content. Regarding the assessment of preliminary efficacy, the inclusion of the nested neurophysiological study using EEG will further investigate whether FULLSENSE has the potential to modulate brain connectivity related to key psychological processes associated with sexual well-being, offering valuable insights into the intervention’s mechanisms of action. Furthermore, a preliminary usability study was conducted to gather feedback from individuals experiencing sexual dysfunction regarding the program’s content, structure, format, and user experience. This process contributed to refining the program, ensuring greater coherence and alignment with the needs of the target population. Also, the program follows a transdiagnostic structure, incorporating multimodal intervention strategies, namely mindfulness-based exercises that address multiple diagnostic categories (Greeson, Garland, & Black, 2014) in different populations experiencing sexual dysfunction. We, also, highlight that the gender and orientation agnostic design is a strength that ensures maximal accessibility to a broad range of adults with sexual difficulties.

As aforementioned, this feasibility pilot trial has several strengths, including its RCT design, the inclusion of diverse sexual dysfunctions (both male and female), the use of validated outcome measures, and its comprehensive and transdiagnostic nature. Nevertheless, some limitations must be acknowledged. While adequate for feasibility testing, the sample size may limit the generalizability of the findings and preclude definitive conclusions about efficacy. Initially designed for evaluative training courses, the platform may not be optimally suited for the program’s learning and reflection exercises, potentially impacting user experience, especially for smartphone users. Consequently, recruitment and retention of participants may present challenges, so future optimization of the platform for smartphone use might also be crucial. A key limitation of this protocol, inherent to its pilot nature, is the **small sample size (N = 70)**. While sufficient for assessing feasibility and generating preliminary effect sizes, the study is **not powered to draw definitive inferential conclusions** regarding the efficacy of the FULLSENSE intervention. The results must therefore be interpreted cautiously and strictly within the context of **viability and preparatory data** for a larger trial Also, the participatory design approach did not include its primary end users, which may influence acceptability and feasibility. We acknowledge the limitation that, due to its general design, the program may not fully reflect the specific, nuanced experiences of all sexual and gender minority groups, which may influence individual engagement. We clarify that future qualitative research will be essential to explore these differences in depth.

The FULLSENSE feasibility pilot trial promises valuable insights into an accessible, evidence-based online intervention for sexual dysfunction, contributing to digital sexual health solutions. The mixed-method approach will deepen understanding of FULLSENSE’s acceptance and implementation. By adopting a comprehensive approach to sexual health, and sexual dysfunction in particular, the FULLSENSE feasibility pilot trial might ultimately contribute to realizing sexual health as a fundamental right (Van Lankveld et al., 2021). Upon completion of the **FULLSENSE Pilot RCT**, the research team is committed to preparing a separate follow-up manuscript reporting the **feasibility outcomes, participant engagement metrics, and preliminary effect sizes**, with the goal of submitting it to a high-impact journal immediately. This sequential dissemination plan ensures that the scientific community first benefits from the **transparent methodology (Protocol)** and subsequently gains access to the **empirical results** necessary for planning a future, fully powered trial.
